**Methods/design:**

The aim of the present study is to evaluate the cost-effectiveness of multidisciplinary team training in a medical simulation centre in the Netherlands to reduce the number of medical errors in obstetric emergency situations. We plan a multicentre randomised study with the centre as unit of analysis. Obstetric departments will be randomly assigned to receive multidisciplinary team training in a medical simulation centre or to a control arm without any team training.

The composite measure of poor perinatal and maternal outcome in the non training group was thought to be 15%, on the basis of data obtained from the National Dutch Perinatal Registry and the guidelines of the Dutch Society of Obstetrics and Gynaecology (NVOG). We anticipated that multidisciplinary team training would reduce this risk to 5%. A sample size of 24 centres with a cluster size of each at least 200 deliveries, each 12 centres per group, was needed for 80% power and a 5% type 1 error probability (two-sided). We assumed an Intraclass Correlation Coefficient (ICC) value of maximum 0.08.

The analysis will be performed according to the intention-to-treat principle and stratified for teaching or non-teaching hospitals.

Primary outcome is the number of obstetric complications throughout the first year period after the intervention. If multidisciplinary team training appears to be effective a cost-effective analysis will be performed.

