## Methods/Design

The proposed research concerns a multicentre randomised controlled trial of obstetric departments in the Netherlands. These obstetric departments will be randomly assigned to receive multidisciplinary team training in a medical simulation centre or to a control arm without any team training.

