### Recruitment

We invited several teaching and non-teaching hospitals in the Netherlands to participate in this randomised study. We excluded hospitals which already have frequently multidisciplinary team training for its care workers, as defined by more than once every year. Randomisation will be performed through a database which is hosted at the Academic Medical Centre (AMC) in Amsterdam. Randomisation will be 1:1 for intervention and control group and it will be stratified for teaching or non-teaching hospital because we expect differences in outcomes in teaching and non-teaching hospitals.

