### Statistics

#### Sample size

The composite measure of poor perinatal and maternal outcome in the non training group was thought to be 15%, on the basis of data obtained from the National Dutch Perinatal Registry and the guidelines of the Dutch Society of Obstetrics and Gynaecology (NVOG). We anticipated that multidisciplinary team training would reduce this risk to 5%. A sample size of 24 centres with a cluster size of each at least 200 deliveries, each 12 centres per group, was needed for 80% power and a 5% type 1 error probability (two-sided). We assumed an Intraclass Correlation Coefficient (ICC) value with a maximum of 0.08. Because there is an uncertainty about the complication rate and perhaps this is lower than expected a sample size of 1000 deliveries per hospital was taken. In conclusion we will try to randomise 24 obstetric departments in the Netherlands with an one year follow-up.

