#### Data analysis

Our primary (base-case analyses) will be performed according to the intention-to-treat principle and stratified for teaching or non-teaching hospital. A baseline analysis will be performed to examine the comparability of groups at baseline for both costs and outcomes. To investigate whether data are normally distributed a Kolmogorov-Smirnov test will be performed. Despite the usual skewness in the distribution of costs, the arithmetic means will be generally considered the most appropriate measures to describe cost data. Therefore arithmetic means (and standard deviations) will be presented. In case of skewness of the cost data, non-parametric bootstrapping will be used to test for statistical differences in costs between the intervention and control group. Non-parametric bootstrapping is a method based on random sampling with replacement based on individual data of the participants. The bootstrap replications will be used to calculate 95% confidence intervals around the costs (95% CI), based on the 2.5th and 97.5th percentiles. If cost data are distributed normally, t-tests will be used. The Incremental Cost-Effectiveness Ratio (ICER) will be determined on the basis of incremental costs and effects of team training compared with non-team training. The cost-effectiveness ratio will be stated in terms of costs per outcome rate, the cost-utility ratio will focus on the net cost per QALY (Quality Adjusted Life Year) gained. The robustness of the ICER will be checked by non-parametric bootstrapping (1000 times). Bootstrap simulations will also be conducted in order to quantify the uncertainty around the ICER, yielding information about the joint distribution of cost and effect differences. The bootstrapped cost-effectiveness ratios will be subsequently plotted in a cost-effectiveness plane, in which the vertical line reflects the difference in costs and the horizontal line reflects the difference in effectiveness. The choice of treatment depends on the maximum amount of money that society is prepared to pay for a gain in effectiveness, which is called the ceiling ratio. Therefore, the bootstrapped ICERs will also be depicted in a cost-effectiveness acceptability curve showing the probability that team training is cost-effective using a range of ceiling ratios.

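### The economic analysis resamples individual participants, or uses plain t-tests, although hospitals are randomised, so cost and ICER uncertainty is understated by an amount that depends on an unstated cost ICC

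*Protocol article*

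**What the plan says.** The Methods/Design opening of the protocol article assigns whole obstetric departments to training or control. Recruitment adds: "Randomisation will be 1:1 for intervention and control group and it will be stratified for teaching or non-teaching hospital". The abstract states: "We plan a multicentre randomised study with the centre as unit of analysis". The Sample size section follows that logic, with 24 centres, 12 per arm, and an ICC of at most 0.08.

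The Data analysis section is mostly about the economic evaluation. For skewed costs it tests the difference by non-parametric bootstrapping, which it describes thus: "Non-parametric bootstrapping is a method based on random sampling with replacement based on individual data of the participants". Percentile 95% limits for costs come from these replications. Bootstrapping, 1,000 times, also supplies the ICER uncertainty, the points on the cost-effectiveness plane and the acceptability curve. The other branch reads: "If cost data are distributed normally, t-tests will be used". From Economic evaluation to the end of Data analysis there is no hospital-level resampling, multilevel model or other allowance for correlation within hospitals. The only hospital feature is stratification by teaching status.

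**The concern.** Deliveries in one hospital share staff, case mix, admission policy and unit costs, so their costs and outcomes are correlated. When hospitals are allocated, the chance difference between arms contains the variation between 24 hospitals. Resampling individuals reproduces only the variation between individuals, as if each delivery had been randomised. A t-test on individual costs has the same fault, so neither branch of the plan avoids it.

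Three outputs are affected. The cost interval is too short. The cloud on the cost-effectiveness plane is too tight. The acceptability curve, which is a probability and has no width, is pushed towards 0 or 1. The abstract gives cost-effectiveness as the aim and ties its recommendation on implementation to it, so unwarranted certainty here would feed directly into the conclusion.

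**Working it through.** **Inputs from the protocol article.** Sample size section: 15% versus 5%, 80% power, two-sided 5%, 12 centres per arm, at least 200 deliveries per centre and then 1,000 adopted, ICC at most 0.08. The ICC for costs is not given; I assume 0.001 to 0.08.

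**Step 1: reproduce the plan's own figure.** For independent deliveries, with pooled variance under the null and no continuity correction:

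n per arm = [1.96 × √(2 × 0.10 × 0.90) + 0.842 × √(0.15 × 0.85 + 0.05 × 0.95)]² / 0.10² = 140.1, rounded up to 141.

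Design effect = 1 + (200 − 1) × 0.08 = 16.92. Then 141 × 16.92 = 2,386 deliveries per arm, and 2,386 / 200 = 11.93, which rounds up to the stated 12 centres per arm. The plan therefore inflates its sample about 17-fold for clustering, and its economic analysis then makes no allowance for it.

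**Step 2: size of the error.** With m deliveries per hospital, the true standard error divided by the individual-level one is r = √(1 + (m − 1) × ICC). A nominal 5% test then rejects under no difference with probability 2 × [1 − Φ(1.96 / r)].

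| Assumed ICC | r, m = 200 | False positives | r, m = 1,000 | False positives |
|---|---|---|---|---|
| 0.001 | √1.199 = 1.1 | 7% | √1.999 = 1.4 | 17% |
| 0.01 | √2.99 = 1.7 | 26% | √10.99 = 3.3 | 55% |
| 0.08 | √16.92 = 4.1 | 63% | √80.92 = 9.0 | 83% |

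Coverage of the nominal 95% interval is one minus the false-positive rate: 83%, 45% and 17% down the last column, after rounding. At m = 1,000 the factor falls below 2 only if 1 + 999 × ICC < 4, that is, for an ICC under about 0.003.

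**Step 3: check by simulation.** Skewed costs, 12 hospitals per arm, 1,000 deliveries each, no true difference, 400 replicates, with the individual-level bootstrap replaced by its normal limit. It rejected in 15%, 55% and 82% of replicates at ICC 0.001, 0.01 and 0.08, in line with the table.

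**Step 4: is a simple hospital bootstrap enough?** In the same simulation, the percentile bootstrap of hospital means rejected in about 9%. Resampling within arm and stratum, with 6 and 6, 4 and 8, or 3 and 9 hospitals per arm in the two strata, also gave about 9%. Far better, but still above 5%: resampling k units understates their variance by (k − 1)/k, and percentile limits make no allowance for few degrees of freedom.

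**The case against.** The strongest reply is that the quoted sentence only explains what bootstrapping is, in an article that condenses a fuller plan, and that the abstract's statement on the unit of analysis governs throughout. This does not rescue the text. The sentence names what is resampled, and on its plain meaning the individual data belong to women and infants, whose resource use the Cost analysis section measures. An analyst who follows it gets the wrong standard error. If hospitals were meant, the sentence still has to be changed.

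Other objections limit the size, and they stand:

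- A reader might infer that the intervals are bound to be several times too narrow. The documents do not support that. The 0.08 is a maximum, set for the clinical composite and not for costs. At an ICC of 0.001 the factor is only 1.1 to 1.4.
- The relevant ICC is the one left within teaching strata. Stratification removes some between-hospital variation, though not the differences among hospitals of the same type.
- The 12-month resource use is measured only for infants in suboptimal health at discharge, so m for that component is well below 1,000 and its design effect smaller.
- A reader might extend the fault to the analysis of the primary complication outcome. The quoted passage concerns costs and the ICER and does not settle that analysis.
- The economic analysis goes ahead only if training proves effective, and the article disclaims power calculations for it. That limits when the error takes effect; it does not make the intervals valid.

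A reader might also fault the Kolmogorov-Smirnov test that chooses between the branches. It is incidental, since both branches share the same defect.

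**Conclusion.** The economic analysis as written uses the wrong unit of inference and conflicts with the article's own statement on the unit of analysis. The direction of the error is clear for any positive correlation within hospitals: intervals and the ICER cloud too narrow, acceptability probabilities too extreme. Its size is conditional, from about 1.1 (m = 200, ICC 0.001) to 9.0 (m = 1,000, ICC 0.08) in standard error. The figures assume hospitals of equal size, cost data on every delivery and no reduction of the ICC by stratification. Even at an ICC of 0.001, the false-positive rate with 1,000 deliveries per hospital would be about three times nominal (17% against 5%). This should be corrected before the economic analysis is run.

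**What to change.** State in Data analysis that the hospital is the unit of inference for the cost difference, the ICER, the plane and the acceptability curve. Two routes serve:

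- Resample whole hospitals within arm and teaching stratum, keeping each hospital's costs and effects together, with a small-sample correction for 12 hospitals per arm applied to every output and not only to the cost difference.
- Fit a bivariate multilevel model for costs and effects with a hospital effect, again with a small-sample correction.

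Replace the individual-level t-test with a comparison of the 24 hospital means adjusted for teaching status (24 − 2 arms − 1 stratum term = 21 degrees of freedom), or with a mixed model. Report the ICC for costs that is found.

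The cost is rewording and some programming, with no new data, patients or centres. The downside is wider intervals and a flatter acceptability curve.

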## Discussion

There are many avoidable deaths in hospitals because the care team is not well attuned. Training in emergency situations is generally followed on an individual basis. In practice, however, hospital patients are treated by a team composed of various disciplines. To prevent communication errors, it is important to focus the training on the team as a whole, rather than on the individual. Team training appears to be important in contributing toward preventing these errors. Obstetrics lends itself to multidisciplinary team training. It is a field in which nurses, midwives, obstetricians and paediatricians work together and where decisions must be made and actions must be carried out under extreme time pressure.

If multidisciplinary team training appears to be effective, this training should be implemented in extra training for gynaecologists.
